### Statistical methods

2.13

Statistical analysis, including a full analysis set based on the intent-to-treat principle and a per-protocol set, will be conducted with SPSS 26.0 software. Continuous variables such as the change in PSQI, HAMA, ISI, SF-12 score compared to the baseline and indicators of sleep diary entries and actigraphy sleep assessment, which is described as mean ± SD or median (interquartile range) will be analyzed by t-test or rank-sum test while categorical variables such as the proportion of patients with reduced medication represented by frequency (composition ratio) will be analyzed by chi-square or Fisher’s exact tests. CIs will be set at 95% with a significance level of 5% (P < 0.05). The success of blinding will be evaluated through Bang’s Index by using the “χ² test” procedure of SPSS 26.0 software. In addition, A subgroup analysis will be conducted based on factors such as age, gender, type of anti-anxiety medication, and type of sedative-hypnotic medication by the “Split File” procedure of SPSS 26.0 software. The confidence interval will be set at 95%, with a significance level of 5% (P < 0.05).

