#### Secondary outcome

2.9.2

The secondary outcomes include the following seven items:

The change in HAMA score compared to the baseline. The Hamilton Anxiety Rating Scale (HAMA), one of the first rating scales to measure the severity of perceived anxiety symptoms, is still in use today and is considered one of the most widely used rating scales. It can effectively compare changes in symptoms before and after treatment to assess the effectiveness of the treatment (26). It will be assessed at weeks 4, 8, 12, and 20.The change in PSQI score compared to the baseline will be evaluated at weeks 4, 12, and 20.The change in Insomnia Severity Index (ISI) score relative to the baseline. It will be evaluated at weeks 4, 8, 12, and 20.Sleep diary entries: Records subjective estimates daily from week 0 to week 8. The recording includes Sleep Onset Latency, Wake After Sleep Onset, Early Morning Awakening, Total Sleep Time, and Sleep Efficiency.The change in the 12-item Short-Form Health Survey (SF-12) score compared to the baseline, which will be evaluated at weeks 8 and 20.Actigraphy sleep assessment: Patients will wear an actigraphy motion recorder for four days during weeks 0 and 8. The recordings will include total sleep time, sleep awakening numbers, wake after sleep onset, average duration of awakening, and sleep efficiency. This device will objectively assess the subjects’ sleep quality.Weekly usage of medication: The usage of sedative-hypnotic medication will be recorded for each group of subjects weekly from week 0 to 20. Adjustments to sedative-hypnotic medication during the treatment and follow-up period will be documented strictly, including the name, dosage, and frequency of the medication.

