### Sample size calculation

2.12

The PASS software (version 15.0.5, NCSS, LLC) was used to calculate sample size with α of 0.05 (two-tailed), power of 80%, and ratio of 1:1. Based on our pilot study, the change in PSQI score of patients with GAD-related insomnia between week 8 and baseline was calculated. For the treatment and control groups, the mean ± standard deviation (SD) was 6.24 ± 3.63 and 3.69 ± 2.45, respectively. The calculated sample size for each group is 33 cases; considering a 20% dropout rate, each group needs 42 participants, totaling 84 participants for both groups.

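### Diary and actigraphy outcomes are named only as indicators and tested without baseline adjustment, so as worded their week-0 recordings are not used

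*Protocol article*

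**What the plan says.** Section 2.9.2 defines the HAMA, PSQI, ISI and SF-12 secondary outcomes as differences from baseline; for the last of these it reads "The change in the 12-item Short-Form Health Survey (SF-12) score compared to the baseline". The two sleep-recording outcomes are described differently. For the diary: "Records subjective estimates daily from week 0 to week 8", followed by a list of parameters. For actigraphy: "Patients will wear an actigraphy motion recorder for four days during weeks 0 and 8", then "The recordings will include total sleep time, sleep awakening numbers, wake after sleep onset, average duration of awakening, and sleep efficiency". Neither entry mentions change. Table 1 confirms that both instruments are used at enrolment and at week 8, the diary also in every week between.

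Section 2.13 keeps the same division. It names "the change in PSQI, HAMA, ISI, SF-12 score compared to the baseline and indicators of sleep diary entries and actigraphy sleep assessment", and says that these variables "will be analyzed by t-test or rank-sum test". No covariate, adjusted model or other use of the week-0 recordings is stated.

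**The concern.** A two-sample t-test or rank-sum test can use a pre-treatment value only through a change score, and the protocol states none for these two instruments. Patients differ lastingly in sleep length and efficiency. If the indicators are compared without reference to week 0, those differences stay in the error term, and whatever gap the arms happened to have before treatment passes in part into the estimate.

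This matters most for actigraphy, of which section 2.9.2 says "This device will objectively assess the subjects’ sleep quality". It is the only objective sleep outcome in a trial whose primary outcome is self-reported. It has just two recording periods, so the week-0 recording has little purpose other than as a pre-treatment reference. The diary is itself subjective, so for the diary the issue is one of precision alone.

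**Working it through.** **Numbers per arm.** The documents give no power figure for diary or actigraphy. Section 2.12 sizes the trial on PSQI with "α of 0.05 (two-tailed), power of 80%, and ratio of 1:1". The difference is 6.24 − 3.69 = 2.55. A t-test with the larger SD, 3.63, in both arms needs 33 per arm (power 80.2%), which matches the plan. Using both SDs, √((3.63² + 2.45²)/2) = 3.10, it would need 25. Dropout: 33/0.8 = 41.25, rounded up to 42. This calculation does not bear on the point; it only supplies n = 33 (evaluable) and n = 42 (randomised).

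**Assumptions not in the documents.** A correlation r between a patient's week-0 and week-8 values (main range 0.4 to 0.7, wider range 0.2 to 0.8), equal SDs at both times, and a true effect of 0.5 SD. Everything is in units of that SD, with normal approximations.

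**Step 1: chance gap at week 0.** SE = √(2/n).
- n = 33: 0.246; 95% range ±1.96 × 0.246 = ±0.48 SD.
- n = 42: 0.218; 95% range ±0.43 SD.

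**Step 2: share of the gap that reaches the estimate.**
- Raw week-8 difference: r × gap. At a gap of 0.48 SD this is 0.19 SD (r = 0.4) to 0.34 SD (r = 0.7).
- Change score: −(1 − r) × gap, in the opposite direction. At the same gap this is −0.29 SD (r = 0.4) to −0.14 SD (r = 0.7).
- Week-8 value adjusted for week 0: about zero on average.

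**Step 3: precision.** Variance relative to the raw comparison is 1 for raw, 2(1 − r) for change and 1 − r² for adjusted. Power = Φ(0.5/SE − 1.96), where SE = √(2/n) × √(relative variance). At 33 per arm:

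| r | Variance, change | Variance, adjusted | Power, raw | Power, change | Power, adjusted |
|---|---|---|---|---|---|
| 0.2 | 1.60 | 0.96 | 53% | 36% | 55% |
| 0.4 | 1.20 | 0.84 | 53% | 46% | 60% |
| 0.5 | 1.00 | 0.75 | 53% | 53% | 65% |
| 0.6 | 0.80 | 0.64 | 53% | 62% | 72% |
| 0.7 | 0.60 | 0.51 | 53% | 75% | 81% |
| 0.8 | 0.40 | 0.36 | 53% | 90% | 92% |

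Adjustment therefore removes 16% (r = 0.4) to 49% (r = 0.7) of the raw error variance; over the wider range, 4% to 64%.

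At 42 per arm and r = 0.6, the raw SE is 0.218 and the adjusted SE is 0.218 × 0.8 = 0.175. Power is Φ(0.5/0.218 − 1.96) = 63% raw and Φ(0.5/0.175 − 1.96) = 82% adjusted.

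**Step 4: error rate given an extreme gap.** With a gap of 1.96 SE and r = 0.6, the raw test statistic under no effect has mean 0.6 × 1.96 = 1.18 and SD √(1 − 0.36) = 0.8. The chance that it exceeds 1.96 in absolute value is about 16%. Smaller gaps give lower rates, and averaged over all gaps the rate is 5%.

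**The case against.** The strongest reply is that the protocol nowhere says that raw week-8 values will be compared. Section 2.13 gives examples in one condensed sentence and names no time point or nightly summary for these instruments; a full protocol or analysis plan may do so. A loose reading could let the opening reference to change govern the whole list, and the introduction says that the focus is on change before and after treatment. This stands to the extent that a raw week-8 comparison is an inference. It does not remove the point. The reference to baseline closes before the indicators are named, section 2.9.2 draws the same line, and the named tests adjust for nothing under either reading.

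A second reply also stands: making these outcomes match the scales would not in itself be an improvement. A change score is noisier than the raw value when r is below 0.5, so it would be wrong to call the raw comparison the least precise option. The same preference for adjustment could be voiced for the scales, but those at least use their baseline.

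Third, the protocol does not present actigraphy as the main check on PSQI and claims no power for it. That is correct; its weight here rests only on its being the single objective sleep measure.

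**Conclusion.** The point holds as a matter of efficiency and clarity for secondary outcomes. As worded, week-0 diary and actigraphy values are collected but not used. Adjusting for them is better than the stated tests whether the indicators are raw values or changes. The gain is a 16 to 49% reduction in error variance against the raw comparison for r of 0.4 to 0.7, or roughly 19 percentage points of power at r = 0.6 and a 0.5 SD effect. Both r and the effect are assumptions; at r = 0.2 the gain is negligible (4%).

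A reader might infer that the planned comparison is biased or has an inflated false-positive rate. The documents do not support that: randomisation keeps it unbiased with 5% type I error overall, and the 16% in step 4 holds only for a week-0 gap at the edge of its 95% range. Nor can one say that the sponsor has decided to discard the week-0 data, since the wording leaves the derived variable open. The primary PSQI analysis is not affected.

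**What to change.** In section 2.13, state that each diary and actigraphy indicator is reduced to one value per patient per period (the mean of the recorded nights or days), and that the arms are compared at week 8 by a linear model with the patient's own week-0 mean as covariate, reporting the adjusted difference with its 95% CI. For the diary, a mixed model on the weekly means for weeks 1 to 8, with the week-0 mean as covariate, is an option.

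The cost is one sentence and a few lines of syntax in the SPSS software already named. No new data, visits or patients are needed, because week-0 recordings are already scheduled. The change should be made before anyone sees outcome data by arm, so that the handling of baseline is not chosen with the results in view.

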### Quality control, data management, and monitoring

2.14

Before treatment, a licensed acupuncturist with a minimum of 5 years’ clinical experience will receive rigorous standardized training in acupoint locations, manipulation techniques, using EA devices, and using appropriate patches for EA and sham EA. Researchers will receive standardized training on the study protocol, standard operating procedures, and scale evaluation to enhance research validity. We designed a Case Report Form specifically for this trial, which was evaluated and recorded by one researcher, stored at the hospital. An extensive data management plan will be developed, encompassing data collection, entry, and handling. To ensure accuracy, data will be entered independently by one researcher, and then data will be confirmed by another researcher. Data quality and research progress will be checked regularly by research assistants and supervised by monitors. The monitoring committee comprises individuals well-versed in clinical practice, research methodologies, and statistics. It operates independently from the study team, maintaining no direct involvement in the trial’s execution. Their responsibilities encompass overseeing trial conduct, decision-making processes, and ensuring the integrity and safety of the gathered data every 6 months.

### Trial status

2.15

The intended trial period is from April 2024 to February 2025. This clinical trial is now recruiting participants. The clinical trial registry will be updated with key protocol changes upon report publication. The study’s findings will be disseminated through peer-reviewed journals or presented at scholarly conferences. Patient data will be anonymized to safeguard participant confidentiality before publication.

## Discussion

3

The symptoms of GAD accompanied by insomnia significantly impair the cognitive and social functioning of patients, imposing a substantial burden on individuals, families, and society (43). Treating GAD with co-occurring insomnia is particularly challenging, with low rates of complete remission (16). Acupuncture, as one of the most important external treatment techniques within traditional Chinese medicine (TCM), is widely applied in the treatment of insomnia and other mental disorders (42, 44, 45), with advantages such as significant efficacy, ease of operation, and few side effects. Previous research (33) demonstrated that compared to the sham acupuncture group, acupuncture can significantly improve anxiety for perimenopausal women with GAD. Another research (46) found that adding acupuncture to standard medication treatment for GAD significantly reduced HAMA and PSQI scores after four weeks of treatment, suggesting that integrating acupuncture into the treatment regimen for GAD with insomnia can significantly alleviate anxiety symptoms and improve sleep quality. Comparative study (40) on the efficacy of EA versus traditional acupuncture in treating anxiety symptoms have found that both methods rapidly reduce anxiety levels, as evidenced by reductions in Beck Anxiety Inventory, GAD scale, and overall anxiety levels, independent of anti-anxiety medication use. De qi, an essential prerequisite for optimal acupuncture efficacy (47), constitutes a multisensory phenomenon experienced jointly by patients and practitioners during needling interventions. During De qi elicitation, patients typically report numbness, dull ache, heaviness, regional pain, or distension at needling sites (48), while the acupuncturist perceives tactile feedback through increased tissue resistance around the needle (49).

However, there is a lack of high-quality randomized controlled trials (RCTs) on the effects of EA on insomnia and anxiety symptoms in patients with GAD, as well as on the efficacy during follow-up periods. To enhance the reliability of results and minimize bias, we will implement several quality control measures. First of all, both real and sham acupuncture treatments will employ an identical auxiliary device (ZL 2023 20605629.3), which is visually indistinguishable to meet blinding requirements and promote better patient compliance. Previous clinical studies (50) have validated this manipulation of sham EA as feasible. Secondly, a comprehensive evaluation of patients’ sleep quality will be conducted using both objective and subjective measures, including PSQI, ISI, sleep diaries, and actigraphy sleep assessment, which will provide a more comprehensive understanding of patients’ sleep patterns. Thirdly, the HAMA scale was utilized to evaluate anxiety levels, while the assessment of patients’ quality of life was also conducted. This comprehensive assessment will provide a thorough evaluation of sleep, anxiety, and overall living conditions in patients with GAD-related insomnia.

Nevertheless, there are limitations to the current study design. First, this trial is not conducted as a multicenter study but is limited to patients recruited from a single hospital in one city, which may raise concerns about bias due to regional factors. Moreover, given the inherent characteristics of acupuncture interventions, such as the needle passing through the skin and the technique used to elicit the “De qi” sensation, it is not feasible to implement a double-blind method. Thirdly, the mechanisms by which acupuncture improves the insomnia and anxiety symptoms of patients with GAD are not yet well understood, and further experiments are needed to uncover the underlying mechanisms.

## Conclusion

4

The current research seeks to determine the efficacy and safety of EA for patients with GAD-related insomnia by contrasting it with sham EA. This assessment utilizes both subjective and objective indicators and scales, aiming to establish an objective, scientific rationale for clinical treatment and application.
